# A safety study of transumbilical single incision versus conventional laparoscopic surgery for colorectal cancer: study protocol for a randomized controlled trial

**DOI:** 10.1186/s13063-015-1067-5

**Published:** 2015-11-30

**Keywords:** Colorectal cancer, laparoscopy, single incision, SILS, rectosigmoid, transumbilical, randomized controlled trial, study protocol

## Abstract

**Background:**

Single-incision laparoscopic surgery (SILS) is an emerging minimally invasive surgery to reduce abdominal incisions. However, despite the increasing clinical application of SILS, no evidence from large-scale, randomized controlled trials is available for assessing the feasibility, short-term safety, oncological safety, and potential benefits of SILS compared with conventional laparoscopic surgery (CLS) for colorectal cancer.

**Methods/Design:**

This is a single-center, open-label, noninferiority, randomized controlled trial. A total of 198 eligible patients will be randomly assigned to transumbilical single incision plus one port laparoscopic surgery (SILS plus one) group or to a CLS group at a 1:1 ratio. Patients ranging in age from 18 to 80 years with rectosigmoid cancer diagnosed as cT1-4aN0-2 M0 and a tumor size no larger than 5 cm are considered eligible. The primary endpoint is early morbidity, as evaluated by an independent investigator. Secondary outcomes include operative outcomes (operative time, estimated blood loss, and incision length), pathologic outcomes (tumor size, length of proximal and distal resection margins, and number of harvested lymph nodes), postoperative inflammatory and immune responses (white blood cells [WBC], neutrophil percentage [NE %], C-reactive protein [CRP], interleukin-6 [IL-6], and tumor necrosis factor-α [TNF-α]), postoperative recovery (time to first ambulation, flatus, liquid diet, soft diet, and duration of hospital stay), pain intensity, body image and cosmetic assessment, 3-year disease free survival (DFS), and 5-year overall survival (OS). Follow-up visits are scheduled for 1 and 3 months after surgery, then every 3 months for the first 2 years and every 6 months for the next 3 years.

**Discussion:**

This trial will provide valuable clinical evidence for the objective assessment of the feasibility, safety, and potential benefits of SILS plus one compared with CLS for the radical resection of rectosigmoid cancer. The hypothesis is that SILS plus one is feasible for the radical resection of rectosigmoid cancer and offers short-term safety and long-term oncological safety comparable to that of CLS, and that SILS plus one offers better cosmetic results and faster convalescence compared to CLS.

**Trial registration:**

ClinicalTrials.gov: NCT02117557 (registered on 16 April 2014).

**Electronic supplementary material:**

The online version of this article (doi:10.1186/s13063-015-1067-5) contains supplementary material, which is available to authorized users.

## Background

### Rationale

Colorectal cancer is one of the most commonly diagnosed cancers worldwide, and adequate surgical excision of the primary tumor is the only curative treatment [1, 2]. As the minimally invasive surgical era evolves and laparoscopic techniques continue to develop, conventional laparoscopic surgery (CLS) has been recommended as an alternative to open surgery for colorectal cancer. Compared with open surgery, CLS provides various advantages, including reduced pain, a shorter hospital stay, and improved cosmetic results [3–6]. Furthermore, many studies have demonstrated that its short-term safety and long-term oncological safety, in terms of DFS and OS, are comparable to those of open surgery [3–9]. These excellent results have encouraged surgeons to find more minimally invasive techniques for colorectal cancer. Recently, many of these efforts have focused on single-incision laparoscopic surgery (SILS).

SILS is performed entirely through one extraction site, typically through the umbilicus, an embryological natural orifice that can conceal a surgical scar [10]. Since it was first reported in 2008, several retrospective studies have suggested that SILS offers potential benefits over CLS for the treatment of colorectal cancer, including a reduced risk of trocar-related complications, reduced postoperative pain, improved convalescence, and improved cosmetic results [10–14]. However, despite its encouraging results, SILS is technically challenging because of the associated limited instrument movement, loss of triangulation, and in-line viewing, and these technical difficulties may lead to prolonged operation time, increased complications, and uncertain oncological outcomes [12, 14–16]. In addition, in the view of Hamabe et al., the technical difficulties of SILS were more evident in cases of sigmoid and rectal cancer, especially when rectal transection and double-stapling anastomosis were performed intracorporeally through the umbilical incision [16]. To minimize the abdominal trauma and the technical difficulties, the use of single-incision plus one port laparoscopic surgery (SILS plus one), which includes an additional port in the right lower quadrant to SILS for sigmoid and rectal cancer, has gained increasing attention from colorectal surgeons [16, 17]. Adding a port in the right lower quadrant can overcome the technical difficulties and is also convenient for drainage, which makes it possible to effectively evaluate and conservatively manage bleeding, anastomotic leakage, and chyle leakage [16, 17].

Many studies have reported that SILS plus one is feasible for colorectal cancer treatment and offers short-term safety comparable to that of CLS [15, 17]. However, the published studies had several limitations, such as a retrospective design, small samples, and poor methodologically quality [15, 17]. There is still no available evidence from large-scale, randomized controlled trials assessing the feasibility, short-term safety, long-term oncological safety, and potential benefits of SILS compared with CLS for rectosigmoid cancer.

### Objective and hypothesis

The objective of this trial is to evaluate the feasibility, short-term safety, long-term oncological safety, and potential benefits of SILS plus one compared with CLS for the radical resection of rectosigmoid cancer in a randomized controlled trial. The hypothesis is that SILS plus one is feasible for the radical resection of rectosigmoid cancer and offers short-term safety and long-term oncological safety comparable to that of CLS. In addition, SILS plus one provides better cosmetic results and faster convalescence compared with CLS.

## Methods/Design

### Setting

This is a single-center, open-label, noninferiority, randomized controlled trial. The trial is being undertaken at Nanfang Hospital of Southern Medical University, Guangzhou, Guangdong, China, which performs 450 colorectal cancer resections per year. Recruitment began on April 16, 2014, and the trial is expected to proceed for 96 months.

### Participants

Patients aged 18 to 80 years with rectosigmoid cancer diagnosed as cT1-4aN0-2 M0 lesions via abdominal computed tomography (CT) and colonoscopy according to the 7th Edition of the American Joint Committee on Cancer (AJCC) Cancer Staging Manual [18] and a tumor size no larger than 5 cm will be further screened for inclusion (Table 1) by a designated investigator.

**Table 1 Tab1:** Inclusion, exclusion, and withdrawal criteria

Inclusion criteria	Exclusion criteria	Withdrawal criteria
• 18 years < age < 80 years	• BMI > 30 kg/m^2^	• Invasion of adjacent structures or distant metastasis
• Tumor located in the rectosigmoid (defined as 10 to 30 cm from the anal verge, measured via colonoscopy or EUS)	• Pregnant or lactating women	• Inability to undergo surgery or anesthesia because of a changing illness state
• Pathological rectosigmoid cancer	• Severe mental disease	• Changing illness state requires an emergency operation
• Clinically diagnosed cT1-4aN0-2 M0 lesions according to the 7th Edition of the AJCC Cancer Staging Manual (measured using abdominal CT and colonoscopy or EUS)	• Previous abdominal surgery (except extraperitoneal surgery)	• Intraoperative colon irrigation
• Tumor size of 5 cm or less	• Emergency operation to treat complications (bleeding, perforation, or obstruction) caused by colorectal cancer	• Serious protocol violations
• ECOG performance status of 0 to 1	• Need for simultaneous surgery for another disease	• Patient required to withdraw
• ASA classification I to III	• Malignant disease within the previous 5 years (except superficial squamous or basal cell cancer of the skin or in situ cancer of the cervix)	
• Informed consent	• Nonspeaker of Chinese or English	

*EUS* endoscopic ultrasonography, *AJCC* American Joint Committee on Cancer, *CT* computed tomography, *ECOG* Eastern Cooperative Oncology Group, *ASA* American Society of Anesthesiologists, *BMI* body mass index

### Recruitment and trial timeline

After being screened for inclusion and exclusion criteria, the potential participants will be verbally introduced to the study by an investigator. A signed written informed consent will be obtained from each patient before his or her inclusion in the study. A copy of the signed consent will be given to the participant, and the original consent will be kept in the hospital. Surgery will be performed within 7 days of patient enrollment or, if it is not, the reason will be recorded in the case report form (CRF). After enrollment, the baseline demographic and clinical characteristics of the participant will be measured preoperatively (Table 2), and any participants who meet the withdrawal criteria (Table 1) will be withdrawn from the trial. The flow of participants and time schedule are presented in Fig. 1.

**Table 2 Tab2:** Preoperative and postoperative outcome parameters and schedule of study visits and follow-up

Measures	Preoperative	Daily in-hospital study visits							Follow-up														
		POD 0^b^	POD 1	POD 2	POD 3	POD 4	POD 5	POD ≥6	M1	M3	M6	M9	M12	M15	M18	M21	M24	M30	M36	M42	M48	M54	M60
Inflammatory parameters (WBC, NE %, CRP, IL-6, TNF-α)	X^a^	X^c^	X^c^			X^c^																	
VAS score			X	X	X		X																
Short-term recovery^d^			X	X	X	X	X	X															
Post-voiding residual urine	X^a^				X																		
EORTC QLQ-C30	X^a^								X	X	X												
EORTC QLQ-CR29	X^a^								X	X	X												
IPSS	X^a^								X	X	X												
BIQ									X	X	X												
Abdominal incision photograph		X							X	X	X												
Physical examination	X^a^								X	X	X	X	X	X	X	X	X	X	X	X	X	X	X
CEA, CA72-4, CA19-9	X									X	X	X	X	X	X	X	X	X	X	X	X	X	X
Chest radiography	X									X	X	X	X	X	X	X	X	X	X	X	X	X	X
Liver ultrasonography										X		X		X		X		X		X		X	
Abdominal and pelvic CT scan	X										X		X		X		X		X		X		X
Colonoscopy or EUS	X										X		X		X		X		X		X		X
Adverse event		X	X	X	X	X	X	X	X	X	X	X	X	X	X	X	X	X	X	X	X	X	X

^a^Preoperative study visits will be scheduled within 7 days before surgery; ^b^The study visit on POD 0 will be scheduled during and after surgery; ^c^Inflammatory parameters will be measured at postoperative 4 hours, 24 hours, and 96 hours after skin suture; ^d^Short-term recovery, including time to first flatus, time to resuming liquid diet and soft diet, time to ambulating independently and discharge. POD, postoperative day; M, month; WBC, white blood cells; NE %, neutrophil percentage; CRP, C-reactive protein; IL-6, interleukin-6; TNF-α, tumor necrosis factor-α; VAS, visual analogue scale; QLQ-C30, Quality of Life Questionnaire-Core 30; QLQ-CR29, Quality of Life Questionnaire-Colorectal 29; IPSS, International Prostatic Symptom Score; BIQ, Body Image Questionnaire; CEA, carcinoembryonic antigen; CA 72-4, carbohydrate antigen 72-4; CA 19-9, carbohydrate antigen 19-9; CT, computed tomography; EUS, endoscopic ultrasonography

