### Outcome measures

#### Primary endpoints

The primary outcome is early morbidity, which will be divided into morbidity observed during operation and morbidity observed within 30 days after surgery. Early morbidity will be assessed on POD 30 and classified according to the Clavien-Dindo classification [36].

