### Data management

Data will be recorded in the CRF by an investigator and reviewed by another investigator for completeness before it is transferred into the trial database. Any missing data will be identified and drawn from source data or from the participants. The CRF will then be transferred into the trial database and double-checked to ensure accurate transfer. Each participant will be given an allocation number according to their randomization. To maintain participant confidentiality, all data will be identified by allocation number, and only the investigators will be able to link the allocation number to the participant’s identification using a list saved separately from the database. All study-related participant information will be stored in a specified investigator’s office in locked filing cabinets. The trial database, photographs and videos will be double saved. In case of withdrawal, follow-up and data collection will continue with the participant’s permission. An investigator will review the database to ensure accurate data collection using descriptive statistics to check for missing data and out-of range values. Any unclear data will be traced to the original medical records. Upon the completion of the trial, all study-related data and trial documents will be archived securely and retained for a minimum of 10 years at Nanfang Hospital.

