### Statistical methods

#### Sample size

The sample size was determined for the primary endpoint: early morbidity measured on POD 30. Based on our database, the early morbidity rate of CLS for colorectal cancer is 15.2 %; for SILS plus one for colorectal cancer, the early morbidity rate is 11.1 %. The sample size was determined according to the following:Hypothesis: the early morbidity of SILS plus one is not higher than that of CLS (noninferiority analysis).We set the noninferiority margin at 10 %.A one-sided analysis with a type I error (α) of 2.5 % and a power (1-β) of 0.80 was assumed.

Based on these assumptions, a sample size of 90 participants per arm was calculated using the NCSS-PASS (11^th^ edition, NCSS, LLC, Utah, USA). Assuming a drop-out rate of 10 %, the total number of participants needed per arm is 99, resulting in a total of 198 participants for the primary aim.

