#### Statistical analysis

The statistical analysis will be performed using SPSS version 13.0 (SPSS, Inc., Chicago, IL, USA). A two-sided p < 0.05 will be considered significant. Descriptive statistics will be used for baseline characteristics. For categorical variables, including the primary outcome, a χ^2^ test or Fisher’s exact test will be applied. For continuous variables, Student’s t test or the Mann-Whitney U-test will be applied. Kaplan-Meier curves and the log-rank test will be used to analyze the OS and DFS differences between the two groups. We do not plan to perform interim analyses. Missing values will not be imputed. Any outcomes of interest analysis will be performed based on the intention-to-treat population and per-protocol population (PPP), and a standard sensitivity analysis will be performed based on the PPP.

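### Mandatory withdrawal from the trial for reasons that can arise in theatre, after the surgeon knows the arm, is not reconciled with the intention-to-treat analysis of early morbidity

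*Protocol article*

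**What the plan says.** The section on recruitment and trial timeline makes withdrawal mandatory: "any participants who meet the withdrawal criteria (Table 1) will be withdrawn from the trial". Table 1 lists six criteria. Among them are invasion of adjacent structures or distant metastasis, "Intraoperative colon irrigation" and "Serious protocol violations". The article does not define the last of these and does not say who applies any of the six.

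Under randomization and blinding, the surgeon receives the group assignment in a sealed envelope the day before the operation. The Discussion accepts that surgeons cannot be blinded.

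The primary outcome is "early morbidity, which will be divided into morbidity observed during operation and morbidity observed within 30 days after surgery".

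Two further statements govern what happens to withdrawn patients:
- Data management: "In case of withdrawal, follow-up and data collection will continue with the participant’s permission". The same section says that missing data will be sought from source data or from participants.
- Statistical analysis: outcomes are analysed in an ITT and a per-protocol population, and "Missing values will not be imputed". The article does not define either population.

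**The concern.** An ITT comparison rests on keeping randomised patients in the arm to which they were allocated, whatever happens next. A rule that takes patients out of the trial for things found or done during the allocated operation works against this. The arm is then known in theatre, and the reason for withdrawal can fall in the same operation as an endpoint event.

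The direction matters in a noninferiority trial. If withdrawn patients left the primary analysis, and if they were mainly SILS plus one patients with complications, the observed morbidity of the experimental arm would fall and noninferiority would be easier to declare. The per-protocol analysis would not expose this, because patients who meet these criteria would be expected to be absent from it too.

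**Working it through.** **1. The passages side by side.** Table 1 together with the recruitment section says the patient leaves the trial. Data management says data are still collected, if the patient permits. Statistical analysis says an ITT analysis is done, without saying whether patients who have left the trial are in it. Two readings are therefore open: withdrawn patients are followed and counted, or they are removed. Nothing in the article chooses between them.

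**2. Timing of the criteria against allocation.**
- Intraoperative colon irrigation: can only occur during surgery, so always after the envelope is opened.
- Invasion or metastasis: timing not stated; it can come to light at the laparoscopic exploration described for both arms.
- Serious protocol violations: open-ended; they can occur during or after surgery.
- Unfitness for surgery or anaesthesia, need for an emergency operation, and patient request: not intraoperative findings.

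**3. The plan's own sample size, reproduced.** Inputs from the Sample size section: "the early morbidity rate of CLS for colorectal cancer is 15.2" %, "for SILS plus one for colorectal cancer, the early morbidity rate is 11.1" %, margin 10 % (read as an absolute difference), one-sided α 2.5 %, power 80 %.

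n = [0.152 × 0.848 + 0.111 × 0.889] × (1.960 + 0.842)² / (0.10 + 0.152 − 0.111)² = 0.2276 × 7.849 / 0.141² = 89.8, so 90 per arm, as stated. Adding 10 % gives 90 × 1.10 = 99, also as stated. The concern does not depend on this figure.

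**4. Illustration of the size.** The documents give no withdrawal numbers, so the counts below are assumed. Further assumptions:
- The true rates sit at the margin, 15.2 % for CLS and 25.2 % for SILS plus one, with 99 randomised per arm.
- No CLS patient is removed.
- Noninferiority is declared when the upper two-sided 95 % limit for the difference is below 10 points.

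With w SILS plus one patients removed, all with an event, the expected observed rate is

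p = (99 × 0.252 − w) / (99 − w).

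The chance of declaring noninferiority is

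Φ( [0.10 − (p − 0.152)] / SE − 1.96 ), with SE = √[0.152 × 0.848 / 99 + p(1 − p) / (99 − w)].

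| w | observed rate p | false noninferiority |
|---|---|---|
| 0 | 25.2 % | 2.5 % |
| 1 | 24.4 % | 3.4 % |
| 2 | 23.7 % | 4.6 % |
| 3 | 22.9 % | 6.1 % |
| 4 | 22.1 % | 8.1 % |
| 5 | 21.2 % | 10.7 % |

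For w = 2: p = 22.948 / 97 = 0.2366, SE = 0.0562, (0.10 − 0.0846) / 0.0562 = 0.274, and Φ(0.274 − 1.96) = 0.046. For w = 5 the result is 10.7 % with CLS kept at 99, and 10.5 % if both arms are set to 94; the difference is immaterial.

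**5. The same calculation under milder assumptions.** Suppose 5 % of the SILS plus one arm is removed. The error is:
- 2.5 % if their event rate equals the arm's 25.2 %;
- 4.2 % if their event rate is 50 %;
- 10.5 % if all of them had an event.

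If two or five event patients are removed from each arm, the error is 2.3 % or 2.0 %, so there is no inflation. If withdrawn patients stay in the ITT set with their POD 30 outcome, it remains 2.5 %.

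**The case against.** A reader might infer that the protocol prescribes dropping endpoint events from the ITT set on the unblinded surgeon's judgement, and that the ITT and per-protocol sets share the same exclusions. The documents do not support that.
- Data collection continues after withdrawal with permission, and missing data are sought in source records. An outcome is lost only if permission is refused or the records fail.
- No sentence removes withdrawn patients from the ITT set. Its definition may stand in the full protocol or analysis plan, which are not shown.
- No one is named as judge of the criteria. That the surgeon decides is plausible for events in theatre, but it is an inference.
- The withdrawal sentence sits in the description of the preoperative step, and three of the six criteria are not intraoperative findings.
- The Discussion's examples of intraoperative morbidity are injuries and bleeding, neither of which is a withdrawal criterion. Added ports and conversion to open surgery are allowed, so they are not in themselves violations.
- Nothing ties the 10 % drop-out allowance to Table 1. Reading it as a sign that such withdrawals are expected is speculation.

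All of this stands, and it limits the point to a conflict between stated rules. It does not remove the conflict. The withdrawal sentence refers to Table 1 as a whole, and one entry there is explicitly intraoperative, so a purely preoperative reading would contradict the table. The permission condition applies to every withdrawal, including those the trial itself imposes. An analysis plan can define the ITT set, but it cannot supply POD 30 outcomes that were not obtained.

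**Conclusion.** The point holds as a conflict to be reconciled. The article requires withdrawal from the trial for reasons of which one must, and two others may, arise after the unblinded surgeon knows the arm. It also plans an ITT noninferiority analysis of an endpoint that includes intraoperative morbidity. Continued data collection with permission mitigates this but leaves the ITT status of withdrawn patients open.

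The size cannot be derived from the documents. It ranges from no inflation, when removed patients are typical of their arm or are removed equally from both arms, to an error of about 4.6 % with two removed and 10.5 to 10.7 % with five. Those upper figures are a worst case: every removed patient is a SILS plus one patient with an event, and no CLS patient is removed. They show how few patients would matter at 99 per arm; they do not forecast what will happen.

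**What to change.** Reword Table 1 and the withdrawal sentence in the recruitment section so that meeting one of these criteria after randomisation removes a patient from the per-protocol set only. State that every randomised patient who is operated on stays, in the allocated arm, in the ITT analysis of early morbidity to POD 30. Take the outcome from source records, as the Data management section already provides, unless the patient withdraws consent for the use of data.

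The cost is wording; the sample size does not change. The drawback is that the ITT set will include a few patients who did not receive the planned operation. The per-protocol analysis already planned lets that effect be examined.
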